## 9.4 STATISTICAL ANALYSES

### 9.4.1 GENERAL APPROACH

Following finalization of the protocol, but prior to data lock, the DCOC statistical team will issue a Statistical Analysis Plan (SAP) as a separate document, which will provide detailed analytical plans for the set of analyses outlined below. The statistical team will conduct all statistical analyses following the statistical principles for clinical trials as specified in ICH Statistical Principles for Clinical Trials (ICH Topic E9). The study team will describe and justify any deviations from the planned analyses in the final integrated clinical study report. The study team will present all study data and summary tables for the overall study and by study sites.

Descriptive data summaries for continuous data will include mean and standard deviation or median and interquartile range, as appropriate. The team will also summarize categorical data by using frequency and proportion, and they will investigate any outliers detected during data review and will define in the SAP methods for handling outliers or data transformation.

### 9.4.2 ANALYSIS OF THE PRIMARY ENDPOINT(S)

Determining the utilization of **clinical assessments** (paper assessments in control group and RAMP Reports in intervention group) in rural primary care clinics will be a key parameter necessary for conducting a future main trial. Utilization will be determined by assessing the numbers of completed caregiver reports and teacher reports in each of the groups (intervention and control). Counted reports include any **clinical assessment** including paper assessment or RAMP Report that is submitted to a provider but not the midpoint and endpoint **study assessment** that will be for study purposes only. Any paper assessments submitted for intervention group participants will be counted separately from the RAMP reports and a sensitivity analysis will be performed to gain insight into that data. Data analysis will report mean, standard deviation, median, and interquartile range for each utilization measure overall and stratified by intervention group. Additionally, we will develop a Poisson regression model to compare the number of returned structured reports across the groups. We will report the expected mean number of reports in each group along with their difference with 95% confidence interval (CI).

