| Description of Sites Enrolling Participants: | A total of 4 practice locations will be selected from two ISPCTN awardee sites, with each site recruiting at least 1 practice location for participation. Practices should care for at least 700 patients aged 5-11 years and should regularly diagnose and manage pediatric ADHD. Practices                                                                                                                                                                                               |                                                                                                                                                                                                                                                                                                                                               |

will be designated as rural if they are at least 30 minutes travel distance from a pediatric academic medical center (similar to prior studies) and are located in a city with fewer than 50,000 people. Practices will be designated as underserved if at least 40% of its pediatric patient visits are covered by Medicaid.

The staff at the selected practices are not directly involved in the design, execution, or analysis of this research study and are thus considered not engaged in research activities. However, practice personnel may carry out specific, limited supportive tasks as directed by the site study team, provided these tasks remain appropriately constrained in scope.

**Description of Study Intervention:** The intervention group will be enrolled in the RAMP. The RAMP platform used for this study will be an adaptation of an existing program and will be housed in REDCap, a HIPAA-compliant data collection tool. Caregivers and teachers will receive text-based requests for reports with embedded links to select radio button questionnaires directly on their mobile device (without any login requirement). Questions include current inattention/hyperactivity symptoms, school performance, and any engagement in behavioral therapy. These areas of information are typically considered by providers to aid in decision making regarding medication dose adjustments. Inattention/hyperactivity symptom questions and scoring is taken directly from the Vanderbilt Assessment. These requests for information will be distributed weekly for 4 weeks, then monthly for 2 months.

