**RAMP Reports completed by caregivers:** The RAMP caregiver interface includes monitoring of ADHD symptoms, engagement in behavioral health care visits, and progress in educational settings. These domains of information have been selected as they are typically combined by providers when making decisions regarding medication dose adjustment. The requests for reports will be sent to caregivers as a link in a text message. Upon clicking the link, they will be able to select radio button responses to questions directly on their mobile device (without any login requirement). The RAMP Report requests will be sent weekly for 4 weeks then every month for the remaining 2 months. RAMP Reports will be submittable for 72 hours after initial release. Once a new RAMP Report is available, caregivers cannot go back and complete reports for prior periods.

**RAMP Reports completed by teachers:** Caregivers in the intervention group will provide teachers with a secure, unique link to access the RAMP Platform. This link will be in the form of a QR code which can be printed on paper or emailed directly to the teacher from the caregiver. Teachers will enter the symptom information directly into the platform. The teacher's RAMP Reports are identical to caregiver RAMP Reports, will consist of the first 18 inattention/hyperactivity questions on the Vanderbilt Assessment, and will be requested at the same interval as the caregivers. We will use an approach similar to that used by Power *et al.* The responses to the teacher RAMP Reports will be available to the providers on the RAMP portal. If a child's teacher does not want to use the RAMP platform, the child will not be disqualified. If a child has multiple teachers, the caregiver should choose one teacher to participate, preferably the one that spends the most time with the child.

[figure not shown]

**Provider Report Review:** Providers will be alerted by their preferred means (text or email) when new caregiver or teacher reports are available for review. While providers will have access to the platform at all times, there will be one provider survey to document review for any given week that there is either a caregiver survey, teacher survey or both to review. .

| Record ID | DDP New Items from RDW    | Basic Demography Form | initial Vanderbilt | clinician review | 1 week RAMP | clinician review | 2 week RAMP | clinician review | 3 week RAMP | clinician review |

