## 6.2 MEASURES TO MINIMIZE BIAS: RANDOMIZATION AND BLINDING

Following enrollment, caregiver/child dyads will be randomized into one of two treatment arms:

1. Intervention Arm: will participate in the RAMP for a period of 3 months
2. Control Arm: standard of care determined by the treating healthcare provider; digital education handouts (attention controls) distributed by the study team at the same intervals as the RAMP Report requests in the intervention group

Caregiver/child dyads who complete screening and enrollment procedures will be randomized using a stratified randomization scheme together with a varying permuted block randomization. Enrolled caregiver/child dyads from the practices will be randomly assigned to RAMP (intervention) or standard of care (control) at a 1:1 allocation ratio. Randomization will be stratified by practice (i.e., randomized within practices) to control for potential differences in study population or differences in management. Secure, practice-specific randomization lists will be generated for each site to use when randomizing a participant. At enrollment, the research coordinator will assign randomization assignments in sequential order, pulled directly from the list. Due to the nature of the intervention, it is not possible for blinding of treatment assignments to be performed in this study. All providers will receive Best Practice Education based on the 2019 AAP clinical practice guidelines, including the recommended frequency of for symptom gathering that is the basis for the planned schedule of RAMP Report requests. Therefore, providers caring for children assigned to the control group may attempt to meet this schedule. However, they will still face hardships inherent to paper forms.

Research coordinators will also make note if any paper symptom assessments are returned for the intervention arm in addition to the RAMP reports. A [study-specific assessment](#) will be done, at 90 days and will serve as a marker of retention.

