### 9.1 STATISTICAL HYPOTHESES

Primary Endpoint:

H1: Use of the RAMP platform will result in significantly greater number of completed **clinical assessments** per participant in the intervention group compared to the control group

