### 9.2 SAMPLE SIZE DETERMINATION

A total sample of 36 participants was agreed in accordance with published guidance for pilot studies. Up to 36 caregiver/child dyads and 20 providers will be enrolled. Our proposed sample size is also consistent with the recommendations of Whitehead and colleagues (2016). Their derived new stepped rules of thumb for a pilot trial sample size vary depending on an estimated standardized effect size for the main efficacy trial; therefore, if we assume a medium Cohen's effect (i.e.,  $0.3 \leq \delta \leq 0.7$ ) and 90% power for the main trial, a sample size of 36 participants with 18 randomized to each intervention arm in the pilot study is sufficient.

With a focus on participant recruitment and adherence, a sample size of 36 allows the study team to estimate an expected recruitment rate of 25% and adherence rate of 50%, each within 12-14 percentage points, with a confidence level of 90%. We expect the rate of return of the RAMP Reports to be a comparable rate to the general survey response rate of 52.7%, though it may be higher as the platform aims to function as an engagement tool.

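### The primary Poisson model makes no allowance for under- or overdispersion, so its 95% CI can be too wide or too narrow; naming a robust or arm-specific variance is a cheap improvement

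*Protocol*

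**What the plan says.** Section 9.4.2 sets the primary comparison: "we will develop a Poisson regression model to compare the number of returned structured reports across the groups". The result to be reported is the expected mean count per arm and their difference, with a 95% CI. Section 9.1 attaches a significance claim: "Use of the RAMP platform will result in significantly greater number of completed" clinical assessments per participant in the intervention group than in the control group. No dispersion parameter, robust variance or fallback is named. For the secondary endpoint, by contrast, section 9.4.3 leaves room for another interval method if the data call for it.

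The design fixes how the counts arise:

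- Section 1.1, on the RAMP schedule: "These requests for information will be distributed weekly for 4 weeks, then monthly for 2 months".
- Section 6.1.1, on teacher reports: they "will be requested at the same interval as the caregivers".
- Section 6.1.1, on missed reports: "Once a new RAMP Report is available, caregivers cannot go back and complete reports for prior periods".
- Section 1.1: control families return paper forms on a schedule set by the provider.

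Section 6.2 adds: "Randomization will be stratified by practice (i.e., randomized within practices) to control for potential differences in study population or differences in management". Section 9.4.2 names no practice term. Section 9.2 puts 18 dyads in each arm.

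**The concern.** A Poisson model with its own variance takes the variance of each count to equal its mean. The RAMP count is a bounded sum of yes/no outcomes: 4 weekly plus 2 monthly requests make 6 time points, and two reporters make at most 12 reports per child. Two features pull the variance in opposite directions. The cap, with a return rate near one half, pushes it below the mean. Dependence among reports on the same child (a family that answers nearly everything or nearly nothing, a teacher who never joins) pushes it above. The two balance only by coincidence. The control count comes from a different process, and nothing ties its variance to its mean either.

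At stake are the width of the interval for the primary difference and the error rate of the test behind the section 9.1 hypothesis. Section 9.4.2 describes utilization as a key parameter for the future main trial, so the stated uncertainty matters.

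**Working it through.** **Inputs from the protocol.** 18 dyads per arm (9.2); maximum RAMP count 6 × 2 = 12 (1.1, 6.1.1); expected return rate p = 0.527 (9.2).

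**Inputs assumed, because the protocol does not give them.** Within-child correlation ρ among the 12 reports, from 0 to 0.5. Control count with mean 1.2 or 3 and variance/mean 1 or 2. The 10% follow-up use of structured reports cited in section 2.2 is a use rate, not a count per child, so it does not fix the control mean.

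**The plan's own figure.** Section 9.2 gives precision only for proportions. With n = 36 and 90% confidence, 1.645 × √(0.25 × 0.75/36) = 11.9 points and 1.645 × √(0.5 × 0.5/36) = 13.7 points, which agrees with the stated 12-14 points. No precision is stated for the Poisson comparison.

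**RAMP arm.** Mean = 12 × 0.527 = 6.32. With correlated reports (beta-binomial), variance/mean = (1 − p)(1 + 11ρ) = 0.473 × (1 + 11ρ). The ratio of Poisson SE to true SE is 1/√(variance/mean). The two agree when 0.473 × (1 + 11ρ) = 1, that is ρ = (1/0.473 − 1)/11 = 0.101.

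**Coverage of the nominal 95% CI for the difference in means.** 20,000 simulated trials per scenario, 18 per arm. The Poisson interval uses √(mean₁/18 + mean₀/18) with multiplier 1.96. The arm-specific interval uses each arm's sample variance with multiplier 2.03. Control scenarios: A, mean 1.2 and variance/mean 1; B, mean 1.2 and variance/mean 2; C, mean 3 and variance/mean 2.

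| ρ | RAMP variance/mean | Poisson SE / true SE (RAMP arm) | Poisson, A | Poisson, B | Poisson, C | Arm-specific, A to C |
|---|---|---|---|---|---|---|
| 0 | 0.47 | 1.45 | 99.2% | 98.1% | 95.2% | 94.1-95.1% |
| 0.05 | 0.73 | 1.17 | 97.4% | 95.9% | 93.4% | 94.4-94.9% |
| 0.1 | 0.99 | 1.00 | 95.0% | 92.9% | 91.4% | 94.6-95.0% |
| 0.2 | 1.51 | 0.81 | 89.6% | 87.4% | 86.9% | 94.1-94.8% |
| 0.3 | 2.03 | 0.70 | 84.6% | 82.9% | 83.4% | 94.2-94.7% |
| 0.5 | 3.07 | 0.57 | 75.7% | 74.6% | 76.3% | 94.2-94.7% |

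**Half-widths in scenario A.** The Poisson half-width is about 1.96 × 0.646 = 1.27 reports whatever ρ is. The arm-specific half-width is 2.03 × 0.478 = 0.97 at ρ = 0, 2.03 × 0.768 = 1.56 at 0.2 and 2.03 × 1.066 = 2.16 at 0.5.

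**Milder dependence.** If the only dependence is that some teachers never take part, RAMP variance/mean is 0.81 (25% of teachers) or 1.00 (50%). If correlation acts only within each reporter, 25% of teachers do not take part, and the control count has mean 1 and variance/mean 2, Poisson coverage is 95% at ρ = 0, 90% at 0.2 and 83% at 0.5.

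**Test.** With the same capped count in both arms at p = 0.527, the nominal 5% Poisson test rejects 0.5% of the time at ρ = 0, 4.9% at 0.1, 11% at 0.2 and 27% at 0.5. This is illustrative only, since control counts have no cap at 12.

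**The case against.** The strongest reply is that sections 9 and 9.4.1 leave detailed plans to a SAP that is not shown, and that Poisson regression with robust standard errors is still Poisson regression. The wording does not rule out a valid analysis, and the variance estimator and covariates are ordinary SAP content. This stands in part: the primary interval cannot be called wrong as written, and the missing practice term is not an error in itself. It does not dispose of the point. Section 9.4.1 says the SAP will detail the analyses outlined in the protocol, that outline names Poisson, and nothing in it requires a variance suited to these counts.

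A reader might go further and infer that the interval is most likely too narrow, with real coverage of 70-85%. The protocol does not support that. It gives no correlation or dispersion, the cap alone makes the interval too wide, and coverage of 85% or less needs ρ of about 0.3 or more. Nor are participants clustered within families: section 5.1 allows one child per household, so the dependence is among reports on one child. The cap of 12 applies to RAMP Reports only.

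The practical effect may also be modest. With means of 6.3 and 1.2 the difference is 5.1, and a half-width of 1.27 or 2.16 excludes zero either way. Section 9.4.2 also requires standard deviations and interquartile ranges by arm, so dispersion will be visible, and section 9.4.9 adds rank-sum comparisons that need no Poisson variance. The protocol does not say that the main trial will be sized from this interval.

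**Conclusion.** The point holds in a limited form. Section 9.4.2 names a Poisson regression for the primary comparison without allowing for under- or overdispersion, while the design makes equality of variance and mean a coincidence in the RAMP arm and an unsupported assumption in the control arm. The model-based interval is conservative if reports on a child are nearly independent, about right near a correlation of 0.1, and increasingly too short above that. The size and direction rest on the assumed correlation, the 52.7% return rate and the assumed control counts; the data will settle them, not the protocol. An arm-specific variance holds close to 95% over the whole range examined, so the choice need not wait for that answer. This is a cheap improvement, not an error that invalidates the analysis.

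**What to change.** In section 9.4.2, or in the SAP with a pointer from it, keep the Poisson (log-linear) model for the mean and add that the 95% CI and the test use a small-sample-corrected robust (sandwich) variance or an arm-specific variance. Include practice (4 levels), the randomization stratum, as a factor, and obtain the difference in mean counts by standardization over practice. A within-practice permutation test can serve as a check.

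The cost is a sentence or two of text and a software option. No data collection or sample size changes. The interval may come out wider than the model-based one; if reports prove nearly independent it will come out narrower.

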### 9.4.3 ANALYSIS OF THE SECONDARY ENDPOINT(S)

The secondary endpoint, proportion of provider review surveys with at least one available RAMP Report where review is documented, is only relevant to the subset of participants randomized to the RAMP intervention group. There is no formal hypothesis testing for this secondary objective. The proportion of provider review surveys with at least one available RAMP Report where review is documented will be estimated along with the corresponding 95% confidence interval using the Wilson score interval or other method appropriate to the data characteristics.

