| Objectives:                                  | Primary Objective:                                                                                                                                                                                                                                                                                                                                                                                                                                                                         | Evaluate completion of clinical assessments by caregivers and teachers.
Aim 1. Evaluate the number of clinical assessments (paper assessments in control and RAMP Reports in intervention) per participant that are completed by caregivers and teachers and returned to providers for ADHD management. |
|                                                     | Secondary Objective:                                                                                                                                                                                                                                                                                                                                                                                                                                                                       | Evaluate provider acceptability of the RAMP through utilization measures.
Aim 2. Evaluate the proportion of all submitted RAMP Reports that are reviewed by providers.                                                                                                                                                |

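### The only interval named for the provider-review endpoint treats repeated surveys as independent and is too narrow if a provider's surveys are positively correlated

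*Protocol*

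**What the plan says.** Section 9.4.3 defines the secondary endpoint as the "proportion of provider review surveys with at least one available RAMP Report where review is documented". It applies to the intervention arm only. The proportion is to be "estimated along with the corresponding 95% confidence interval", computed "using the Wilson score interval or other method appropriate to the data characteristics". The section adds: "There is no formal hypothesis testing for this secondary objective".

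The structure of the data is set elsewhere in the protocol:

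- Section 6.1.1 (Provider Report Review): "there will be one provider survey to document review for any given week" in which a caregiver report, a teacher report or both are waiting. Requests go out at four weekly and two monthly time points.
- Section 9.2: "Up to 36 caregiver/child dyads and 20 providers will be enrolled", and "a sample size of 36 participants with 18 randomized to each intervention arm in the pilot study is sufficient".
- Section 1.1 words Aim 2 per report: "Evaluate the proportion of all submitted RAMP Reports that are reviewed by providers". The endpoint in sections 1.1, 3 and 9.4.3 is per survey.

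Clustering by child, provider or practice is not mentioned for this endpoint.

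**The concern.** A Wilson interval is valid for independent yes/no outcomes. Here the outcome is whether a provider documents a review, and the same provider is asked repeatedly: up to six times per child, and more if several of that provider's patients are in the intervention arm. The endpoint is meant to capture provider acceptability, and section 3 notes that review may be hard to fit into usual workflow. Both suggest a trait of the provider or practice, so positive correlation among one provider's surveys is the natural expectation.

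The pooled count of surveys then overstates the information. With no hypothesis test, the estimate and its interval are the whole result for this endpoint, and section 1.1 says the pilot will be used to design the full-scale trial. An interval that is too narrow would make the provider-engagement assumption look better supported than it is.

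**Working it through.** **1. The plan's own precision figure.** Section 9.2 gives 12-14 points at 90% confidence for rates of 25% and 50% with n = 36. The simple formula 1.645 x sqrt(p(1-p)/36) gives 11.9 and 13.7 points, and Wilson gives 11.6 and 13.2. The figure reproduces, but it concerns recruitment and adherence. The protocol gives no precision figure for provider review.

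**2. Inputs from the protocol.**

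- Surveys: 18 children x 6 time points x 1 survey = at most 108.
- Providers: up to 20 in the trial; at most 18 can contribute if each child has one provider. There are four practices.
- Return rate: section 9.2 expects about 52.7%. Applied per time point, 108 x 0.527 = about 57 surveys. If caregiver and teacher return independently, 108 x (1 - 0.473²) = about 84.

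**3. Assumed inputs, not in the protocol.** A review proportion of 70%, the within-provider ICC, and the number of contributing providers.

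**4. Width.** Plain Wilson with 108 surveys at 70% gives 60.8% to 77.8%, a half-width of 8.5 points. For K equal clusters, m = 108/K, design effect DE = 1 + (m - 1) x ICC, and effective n = 108/DE. Example with K = 10 and ICC 0.1: m = 10.8, DE = 1 + 9.8 x 0.1 = 1.98, effective n = 54.5, half-width 11.8 points, ratio 8.5/11.8 = 0.72.

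Plain width divided by adjusted width:

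| Clusters | ICC 0.05 | 0.1 | 0.2 | 0.3 | 0.5 |
|---|---|---|---|---|---|
| 18 | 0.90 | 0.82 | 0.72 | 0.65 | 0.55 |
| 10 | 0.82 | 0.72 | 0.60 | 0.52 | 0.44 |
| 8 | 0.79 | 0.68 | 0.55 | 0.48 | 0.40 |
| 4 (practice level) | 0.67 | 0.55 | 0.43 | 0.37 | 0.31 |

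Fewer surveys soften this. With 57 surveys and 10 providers the ratios are 0.91, 0.83, 0.67 and 0.58 at ICC 0.05, 0.1, 0.3 and 0.5.

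**5. Coverage.** Simulation with beta-distributed provider probabilities (mean 70%) and 18 children with 3 to 6 surveys each (18 x 4.5 = 81 on average). Coverage of the nominal 95% plain Wilson interval:

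- 10 providers: about 90%, 84%, 69% and 57% at ICC 0.05, 0.1, 0.3 and 0.5.
- 6 providers: 87% down to 46% over the same ICCs.
- 18 providers: 94% down to 75%.

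The spread of children over providers matters somewhat. An even spread over 10 providers gives about 91%, 87%, 72% and 62%. With all 108 surveys, coverage with 10 providers is 88% (ICC 0.05), 82% (0.1), 72% (0.2) and 65% (0.3); with 18 providers it is 91%, 88%, 82% and 77%.

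**6. Adjusted half-width.** With 81 surveys the plain half-width is 9.8 points. With 10 providers and ICC 0.1, 0.3 and 0.5, DE = 1 + 7.1 x ICC = 1.71, 3.13 and 4.55, giving half-widths of 12.6, 16.7 and 19.6 points.

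**The case against.** The strongest reply is that the protocol does not commit to the plain interval. Section 9.4.3 allows another suitable method, clustering is a data characteristic, and sections 9 and 9.4.1 leave detail to a separate SAP that is not at hand. A clustered interval would already comply. This stands as far as it goes: a reader might infer that the protocol binds the team to treating surveys as independent, and it does not. But the clause names no alternative and no trigger, and the repeated surveys follow from the design rather than from anything the data will reveal. The one method the protocol names does not fit the unit it has chosen.

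The second reply concerns size. A reader might infer that the interval is about half as wide as it should be, or that it rests on only a few providers. The protocol supports neither. It allows up to 20 providers and gives no ICC. With 108 surveys, a halved standard error needs DE = 4, that is ICC = 3/(m - 1): 0.31 with 10 providers and 0.60 with 18. With 57 surveys and 18 equal clusters it cannot be reached, since 3/2.17 exceeds 1.

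The third reply is that little hangs on the interval: the endpoint is descriptive, and section 6.3 separately summarizes the number of reports reviewed. That is fair and limits the weight of the point.

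**Conclusion.** The point holds in a limited form. The named default ignores repetition within child and provider and is too narrow for any positive within-provider correlation. The direction follows from the design; the size does not. Over assumed ICCs of 0.05 to 0.5 and 4 to 18 clusters with 108 surveys at 70%, the plain interval has about 31% to 90% of the adjusted width. With about 81 surveys and 10 providers, coverage runs from about 90% to 57%. No single factor, such as one half, can be read from the protocol. The open clause softens the fault without removing it, and no test or decision rule depends on the interval. It is worth correcting because the estimate and interval are all this endpoint reports.

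The per-report wording of Aim 2 is a separate, minor leftover. At most 18 x 6 x 2 = 216 reports against 108 surveys means the two proportions can differ, but the endpoint itself is stated consistently per survey.

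**What to change.** Name a provider-clustered interval with a small-sample correction in section 9.4.3 and the SAP. One option is a Wilson interval on the effective sample size (surveys divided by the estimated design effect, floored at 1), using a t quantile on (contributing providers - 1) degrees of freedom in place of 1.96. State what is done if the estimate is 0% or 100%, where the design effect cannot be estimated.

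The small-sample correction matters. In simulations of the 81-survey setting, the version with a normal quantile covered 88-90% with 6 providers and 91-93% with 10. A percentile bootstrap of providers covered 83-84% and 87-89%. In a check with children spread evenly, ICC 0.05 to 0.5 and the between-provider variance K/(K - 1) x sum(x_k - p n_k)²/n² (x_k reviewed of n_k surveys for provider k), the t version covered about 93-98% with 6 providers and 94-97% with 10.

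Beside the interval, report the number of contributing providers and the provider-level proportions. Reword Aim 2 per survey so that it matches the endpoint.

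The cost is a wording change, a few lines of code and a wider interval for a descriptive endpoint.
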